## Abstract

**Background:**

Cardiovascular disease (CVD) prevention is limited by the major challenge of low long-term adherence to effective lifestyle regimens. Arterial stiffness (measured by carotid-femoral pulse wave velocity [cfPWV]) and maximal cardiorespiratory fitness (measured by VO_2_max) are modifiable risk factors for CVD but require sustained lifestyle change. Wearable technology provides continuous measurement and offers a scalable platform to deliver health interventions. A combination of continuous monitoring with a wearable device and an AI-based coach personalized to individual data and preferences could be a powerful, low-barrier tool for achieving sustainable cardiovascular health benefits by directly addressing the adherence challenge.

**Objective:**

We will study the comparative effectiveness of a wearable and an interactive app-based AI coaching intervention promoting moderate exercise in improving gold-standard cfPWV and VO_2_max. This will be compared to a supervised high-intensity interval training (HIIT) group (benchmark with known benefits for VO_2_max) and a control group using only the Oura Ring (passive monitoring). We will also conduct a detailed process evaluation (structured interviews) to study the feasibility and experience of interacting with the AI coach.

**Methods:**

This randomized controlled trial will recruit 165 eligible sedentary participants aged 30 to 65 years. The co-primary outcomes, cfPWV and VO_2_max, are measured at baseline and will be repeated after 12 weeks. Participants are equally randomized into 3 groups: an AI-based coaching group (steady-state exercise), an HIIT group (supervised exercise), and a control group (usual low activity). The AI-based coaching group receives personalized guidance using large language model technology. All participants wear the Oura Ring and are blinded to the cardiovascular health metrics provided by the ring.

**Results:**

The recruitment for the study began in October 2024 and will end when 165 men and women have been recruited. Data collection for the study is scheduled to conclude in early 2026. Data management is ongoing.

**Conclusions:**

This study will evaluate whether a potentially highly scalable, AI-based coaching intervention can achieve comparable gains in cardiovascular structural health (cfPWV) and functional capacity VO_2_max relative to a resource-intensive supervised HIIT benchmark. The findings will provide essential evidence on the use of digital health tools to promote sustainable exercise adherence.

## Introduction

Cardiovascular disease (CVD) is a leading cause of death, disability, and morbidity worldwide [1]. While chronological age is a major determinant of CVD, the key modifiable factors remain lifestyle-related. Two significant, lifestyle-related, modifiable risk factors are cardiorespiratory fitness (measured by maximal oxygen consumption [VO_2_max]) [2] and arterial stiffness (measured by carotid-femoral pulse wave velocity [cfPWV]) [3]. Cardiovascular age (CVA) is an emerging metric, which expresses an individual’s cardiovascular risk in units of chronological age [4]. CVA provides an intuitive and actionable measure of health and is heavily influenced by cfPWV. CVA is also negatively correlated with VO_2_max [5]. Aerobic exercise consistently reduces arterial stiffness [6] and improves VO_2_max, but long-term adherence to exercise regimens remains a major challenge for many individuals.

Wearable technology is an emerging and potentially scalable solution to enable continuous monitoring of one’s health and possibly to overcome the challenge of adopting new health habits, including regular exercise [7]. Several randomized trials have shown that interacting with a large language model (LLM)–based chatbot is efficacious for increasing physical activity [8]. However, these studies rely on stand-alone discussions without real-time context from wearable-derived physiological signals and the ensuing feedback loop for active engagement. Wearable devices such as the Oura Ring use multiple sensors to provide continuous, at-home estimates of, for example, physical activity, CVA, and sleep quality. The rise of AI enables moving from measurement to using the device as a platform for interventional delivery [9]. AI-based coaching may offer continuous, low-barrier, personalized health behavior guidance that is adaptable to the user’s measured data, life circumstances, and preferences, directly addressing the adherence challenge.

In this trial, the AI-based coaching system functions as a consumer-facing digital health intervention aimed at supporting individuals in adopting and maintaining physical activity behaviors known to reduce arterial stiffness. AI-based coaching delivers personalized guidance, motivation, and feedback based on physiological and behavioral data collected by the Oura Ring, together with limited self-reported information. The AI system is intended for use by adults from the general population seeking to improve cardiovascular health outside formal health care settings. Within the trial, the AI system represents one of the behavior change strategies being compared to evaluate its efficacy in reducing arterial stiffness. The AI system does not inform clinical decision-making or patient management. Instead, the AI system provides automated, participant-facing support for lifestyle modification.

The purpose of this randomized controlled trial is to evaluate the effectiveness of an AI-based coaching intervention promoting moderate, steady-state exercise on improving both gold-standard cfPWV and VO_2_max. This takes place via a feedback loop where the user can freely interact with the AI and gain real-time insights drawn from their data. The study uses a 3-arm parallel design with 2 comparisons. The supervised high-intensity interval training (HIIT) group serves as the benchmark—a comparison whose well-documented advantage is a relatively rapid gain in VO_2_max. This group tests what is physiologically possible but might be challenging to adhere to long term, especially in the broad general population. The Oura Ring only group serves as the baseline comparator to isolate the effect of the AI-based coaching beyond the benefits of passive self-monitoring via the wearable. The primary outcomes are the changes in cfPWV and VO_2_max at 12 weeks. Process evaluation (interviews and chat logs) is conducted for understanding the qualitative aspects of feasibility and the mechanism of adherence for the novel AI coach.

## Methods

### Study Design

Guidance with Oura and AI for Reducing Arterial Stiffness (GONDOR-AS) is a 12-week randomized controlled trial (ClinicalTrials.gov identifier: NCT06644014) consisting of three groups (n=55 per group): (1) Oura Ring only (a control group), (2) Oura Ring+HIIT twice a week (*a physiological benchmark*), and (3) Oura Ring+AI-based coaching for steady-state aerobic training (no external supervision). A full structured abstract fulfilling World Health Organization Trial Registration Data Set version 1.3.1 criteria is provided in Checklist 1. This protocol adheres to the SPIRIT (Standard Protocol Items: Recommendations for Interventional Trials) 2013 Statement and SPIRIT-AI (Standard Protocol Items: Recommendations for Interventional Trials–Artificial Intelligence) extension guidelines (Checklist 2).

All groups will be blinded to their CVA/pulse wave velocity (PWV) information but will use identical Oura Ring devices. Apart from the AI-based coaching group, the Oura App experiences will also be identical. The primary comparison in this trial is explicitly between the AI coaching group and the Oura Ring only group. The supervised HIIT group is included as a “physiological ceiling” benchmark to show what is achievable under resource-intensive conditions.

The study will be implemented in collaboration with the Oura company and the Kuopio Research Institute of Exercise Medicine (KuLTu). Patients and the public were not involved in the initial design of this academic-industry collaboration protocol.

### Recruitment of the Study Participants

Data collection for this study was initiated immediately after receiving approval from the Regional Medical Research Ethics Committee of the Eastern Finland Collaborative Area. We use internal recruitment channels of the Kuopio University Hospital, the University of Eastern Finland, and the Savonia University of Applied Sciences to recruit personnel and students from these institutions. Kuopio city recruitment channels, newspapers, and social media (eg, LinkedIn and Facebook) will also be used to recruit participants from the general population. Altogether, 165 participants, aged 30 to 65 years, will be recruited for the study.

### Inclusion and Exclusion Criteria

Inclusion criteria are an age of 30 to 65 years and self-reported moderate-intensity physical activity of <2 hours 30 minutes per week or vigorous-intensity physical activity of <1 hour 15 minutes per week. This agrees with international physical activity guidelines [10] for the minimum amount of recommended aerobic physical activity per week for adults. Self-reported physical activity data are subsequently reviewed by an expert researcher (HP), who verifies and finalizes participants’ activity profile classifications based on the reported information. Exclusion criteria are coronary artery disease, diabetes, uncontrolled hypertension, or another condition, which could compromise the safe participation in the exercise intervention, as evaluated by a physician (KS). Inability to use the Oura Ring (eg, work-related restrictions) will also be considered an exclusion criterion; however, short interruptions (eg, 1- to 2-h work tasks without the ring) are allowed.

If a participant experiences an adverse event or injury that compromises safe participation, their assigned intervention will be discontinued immediately upon review by the study physician (KS). They will remain in the study for final follow-up and be analyzed under the intention-to-treat (ITT) principle (see section *Statistical Analysis*).

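### The inactivity criterion joins its two limits with *or*, so read literally it excludes only people who reach both, which contradicts the stated sedentary population

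*Protocol article*

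**What the plan says.** The protocol article, Inclusion and Exclusion Criteria, sets an age range (30–65) and this activity condition: "self-reported moderate-intensity physical activity of <2 hours 30 minutes per week or vigorous-intensity physical activity of <1 hour 15 minutes per week". On the source of these limits it says "This agrees with international physical activity guidelines", and it names the benchmark taken from them with the phrase "for the minimum amount of recommended aerobic physical activity per week for adults".

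The same section has a researcher review the self-reports, "who verifies and finalizes participants’ activity profile classifications based on the reported information". The exclusions are medical conditions that make exercise unsafe and inability to use the ring. None concerns a high activity level.

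The Abstract (Methods) says the trial will "recruit 165 eligible sedentary participants aged 30 to 65 years" and labels the comparator as "a control group (usual low activity").

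**The concern.** A minimum expressed as 150 minutes of moderate or 75 minutes of vigorous activity is met by reaching either figure. The negation of *A or B* is *not A and not B*, so a person is below the minimum only when both figures are missed. The criterion reverses the inequalities but keeps the *or*. It therefore selects everyone who misses at least one limit, which is a much wider group than people below the minimum.

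Two things are at stake:

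- **Description of the population.** If the rule was applied as printed, the enrolled people need not be sedentary. If a different rule was applied, the article misreports who was eligible. A reader cannot tell which.
- **Room for change.** The Power Calculations section ties the expected cfPWV reduction to the gain in VO2max. The AI coach steers participants towards 2 to 3 hours of steady-state exercise a week, and controls are told to keep their activity unchanged. Someone already doing 5 hours of moderate activity exceeds the coach's target at entry. In the control arm, that person would simply continue at that level.

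**Working it through.** **Step 1: the rule as printed.** Let m be moderate and v vigorous minutes per week. The limits are 2 h 30 min = 150 and 1 h 15 min = 75. The printed rule is m < 150 *or* v < 75. The rule that matches the guideline sentence is m < 150 *and* v < 75. The last column uses a combined limit, m + 2v < 150, whose weight of 2 is the ratio of the protocol's own limits (150/75).

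| m / v (min per week) | *or* (as printed) | *and* | m + 2v, and whether < 150 |
|---|---|---|---|
| 0 / 0 | eligible | eligible | 0, yes |
| 0 / 300 | eligible | not eligible | 600, no |
| 20 / 240 | eligible | not eligible | 500, no |
| 300 / 0 | eligible | not eligible | 300, no |
| 140 / 70 | eligible | eligible | 280, no |
| 150 / 75 | not eligible | not eligible | 300, no |
| 200 / 100 | not eligible | not eligible | 400, no |

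Under *or*, only the last two profiles, which reach both limits, are shut out. The error runs both ways: heavy vigorous training with little moderate activity passes, and so does ample moderate activity with no vigorous activity. Changing to *and* removes the three profiles that are far above the minimum on one intensity. It still admits 140/70, which only a combined limit rejects.

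**Step 2: is the gap closed elsewhere?** The exclusion list has no bar on high activity. The researcher's classification rests on the reported information, and the text does not say that it overrides the criterion. Nothing stated closes the gap.

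**Step 3: what dilution could cost (illustration only).** The inputs from Power Calculations are effect 0.4 m/s, SD 1.4 m/s, pre-post correlation 0.86, two-sided alpha 0.05, and 55 per group including a 10% attrition allowance.

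- The plan's own figure: 193 × (1 − 0.86²) = 193 × 0.2604 = 50.26, stated as 50 per group, then 50 × 1.10 = 55.
- Evaluable per arm after 10% attrition: 55 × 0.9 = 49.5.
- Standard error of the difference: 1.4 × √0.2604 × √(2/49.5) = 0.1436.

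Assume that a share f of recruits is already active and gains exactly nothing, so the mean effect is 0.4(1 − f). Power is then Φ(0.4(1 − f)/0.1436 − 1.96).

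| f (assumed) | effect (m/s) | power |
|---|---|---|
| 0% | 0.40 | 79.5% |
| 10% | 0.36 | 70.8% |
| 20% | 0.32 | 60.6% |
| 30% | 0.28 | 49.6% |

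Neither f nor the zero gain comes from the documents. The required sample size under the plan's own inputs is unchanged.

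**The case against.** The strongest reply is that the intent is plain. The guideline sentence, the word sedentary and the low-activity label all point to people below the minimum, and the *or* probably carries over the guideline's own phrasing. A researcher finalizes each activity classification and would most plausibly catch someone training vigorously for 5 hours a week. A condensed article may also leave the screening procedure to a fuller document. This stands as a reason to think the practical harm may be small. It does not rescue the criterion, which is stated in full and stated wrongly rather than omitted.

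The reply continues that the consequences are partly visible anyway. Baseline activity is recorded by questionnaire and ring, and baseline cfPWV and fitness are named moderators. Conclusions are already declared exploratory. That is fair, though none of it restores lost power or corrects the published rule.

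A reader might infer three stronger things that the documents do not support:

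- **That the trial did enrol trained people, or has lost power.** No enrolment figure by activity level is given, so the power table is hypothetical.
- **That the comparison between arms is biased.** Eligibility is settled before randomization and applies equally to all arms, so the risk concerns dilution and generalizability.
- **That a combined moderate-equivalent limit is required.** It is stricter than correcting the connector, as the 140/70 profile shows, and so goes beyond repairing the error.

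**Conclusion.** The point holds on the text. As printed, the criterion excludes only people at or above both limits. It contradicts its own guideline sentence and the Abstract's description of the population. It is most likely a wording error, and the review step may already apply the intended rule, but the article does not say so.

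The possible consequences are a weaker average effect on cfPWV and VO2max and a misdescribed population. Their size cannot be derived from the documents. The fall in power from about 80% to about 71% (f = 10%) or 50% (f = 30%) depends entirely on the assumed active share and on no gain in those participants.

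This should be fixed, but it is not a fatal defect. Randomization protects the comparison between arms, and with data collection due to end in March 2026 few recruits may remain.

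**What to change.** - **Correct the criterion.** State that both limits must be met: moderate activity under 150 *and* vigorous activity under 75 minutes per week.
- **State the review rule.** Say that the researcher's review applies this same rule. If the site has always required both limits, say so; the change is then a clarification of wording.
- **If anyone was enrolled under the literal *or*:** keep them in the intention-to-treat set and report how many there are. Add one sensitivity analysis excluding participants whose baseline questionnaire fails the corrected rule. Baseline data are collected before randomization, so this exclusion does not depend on the assigned arm.
- **Optional.** A combined limit such as m + 2v < 150 could be considered for a later trial. Imposing it now would tighten eligibility and split the cohort between two rules.

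The cost is a short text change, one count and one extra model run on data already planned. If the rule actually applied changes, the amendment must go to the ethics committee and the registry, as Ethical Considerations requires for eligibility changes. The pool for any remaining recruitment would be slightly smaller.

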### Study Measurements

#### Overview

Study assessments will be arranged in 2 measurement visits, both at baseline and after the 12-week intervention at KuLTu. The Oura Ring will be provided at the first measurement visit approximately 2 weeks before the start of the intervention. This is necessary for Oura’s CVA algorithm to record an individual baseline for each participant. The ergospirometry test will also be performed at the first visit. PWV measurement and randomization will be performed on the second visit approximately 2 weeks after the first visit.

#### Cardiorespiratory Fitness

To determine the intensity of the individually prescribed training program and the efficacy of the exercise intervention, ergospirometry tests will be carried out on a cycle ergometer (Ergoselect 4; Ergoline GmbH) at baseline and after 12 weeks for all 3 study groups. The test will start with a 1-minute sitting period in the saddle followed by a 3-minute warm-up at 0 W. After that, the workload will increase gradually according to an individualized ramp exercise protocol. The same individualized test protocol will be used at baseline and after the 12-week intervention. The test will be supervised by an experienced exercise physiologist, and participants will be verbally encouraged to continue until exhaustion. Respiratory gas exchange, including ventilation and VO_₂_max, will be measured by the breath-by-breath method (Vyntus CPX; Vyaire Medical). Electrocardiography will be recorded (CardioSoft; GE HealthCare) throughout the baseline exercise test.

#### Pulse Wave Velocity and Pulse Wave Analysis

cfPWV measurements will be conducted in the morning following an overnight fast, during which participants will be instructed to abstain from both caffeine and smoking. Measurements will be performed noninvasively using the Complior Analyze system (version 1.9.5; Alam Medical), which is considered a noninvasive gold-standard device for assessing arterial stiffness [11].

Following a 5-minute rest period in the supine position, the carotid pulse in the neck and the femoral pulse in the groin will be palpated. A small mark will be made at the site of the femoral pulse with a marker pen to ensure accurate distance measurement. The surface distance between the carotid and femoral sites will be measured using a flexible infant measuring device (Kern MSC 100; KERN & SOHN GmbH) and subsequently recorded in the Complior software. The device was selected because it measures straight-line distance independent of body shapes, such as particularly large bellies and/or breasts in individuals with obesity. We only measured the distance between the carotid and femoral sites during the first visit to avoid introducing additional within-person measurement error [12].

A tonometric pulse sensor clamp will then be placed at the carotid artery site. The waveform morphology and signal quality will be visually inspected in the Complior software, and the measurement will proceed only when the signal is deemed acceptable. Subsequently, a finger-type sensor will be applied to the femoral pulse site. Pulse waveforms from both locations will be acquired simultaneously, and recordings will be accepted once the software indicates sufficient signal quality (≥95%). Each cfPWV measurement will be repeated at least three times to ensure reliability, and the results will be averaged for analysis.

Pulse wave analysis will be performed noninvasively from the brachial artery using a cuff integrated into the same device. During the entire measurement protocol, participants will also wear the Oura Ring, enabling the concurrent assessment of additional physiological parameters.

#### Other Assessments

Standard demographics (age, sex, and ethnic background according to the United Nations Standard country or area codes for statistical use [M49]) will be collected from all participants, and skin phototype will be evaluated according to the standard Fitzpatrick Scale. These are routinely collected for Oura’s internal photoplethysmography (PPG) signal quality control to ensure that outputs remain consistent across various skin tones. In addition, body composition will be determined by bioelectrical impedance (Inbody 720 body composition analyzer) in the standing position after an overnight fast. Height will be measured in the standing position. Female participants will also be asked about their menstrual cycle phase, as it affects several of their composite scores and PWV measured by the Oura Ring. Previous physical activity levels will be assessed using a modified version of the short form of the International Physical Activity Questionnaire. The International Physical Activity Questionnaire is a set of questionnaires designed to assess physical activity levels in individuals aged 18 to 65 years [13]. All participants will also be asked to complete questionnaires at the beginning and end of the study to assess experiences of body composition measurement (RM4-FM), and exercise motivation and self-efficacy for exercising (Exercise Self-Efficacy Scale [ESES]) in electronic form (attachments labeled “RM4-FM” and “ESES”) made by using survey administration software (Google Forms).

#### Poststudy Interviews

A random subgroup from each study group will be invited to a 1-hour online qualitative interview at the end of the study. The aim of the interview study is to conduct a behavioral process evaluation of the exercise intervention to better understand how participants perceive changes in exercise habits and the use of the Oura Ring to support exercise guidelines in each group. The interviews will be recorded and transcribed verbatim. Approximately 8 participants from each group (N=24) will be recruited for the interviews by invitation as they exit the main study. The study manager will invite participants who have sufficient technological capability to take part in online interviews and will ensure that approximately equal numbers are invited from each study arm. Interactive tools will be used in the interviews to map experiences and general well-being paths during the study period. Participants will be asked to draw or point out their own experience and well-being path using these tools.

